### Statistical Analyses

All statistical analyses for testing efficacy and cost-effectiveness will be done according to the intention-to-treat principle. Additionally, neuroplasticity will be analyzed based on the per-protocol sample, using a minimum number of 12 rTMS-ERP sessions as the threshold for adequate treatment. The significance level will be set at alpha=.05, 2-tailed. Safety data (eg, side effects and serious adverse events) are collected and summarized in the study results. A description of the analyses for the primary, secondary, and exploratory objectives is provided below.

#### Primary Study Parameter

The primary study parameter is the posttreatment effect of the intervention (verum-rTMS vs sham-rTMS) on the primary outcome measure (Y-BOCS I). This effect will be estimated using an ANCOVA model adjusting for baseline Y-BOCS I scores.

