### Setting of the Study

This multicenter trial is carried out in specialized mental health care facilities across the Netherlands. Participants are recruited through multiple channels: outpatient clinics with extensive experience in the treatment of OCD, self-referral, and through the patient organization for Anxiety and OCD. The patient organization was also actively involved in the design of the trial, and one of their representative lived experience researchers participates in the monthly research meetings to support ongoing collaboration and alignment with patient perspectives. The 5 participating sites geographically cover the country, enabling treatment in the catchment area of the participants’ home. These 5 sites are located in Amsterdam (Amsterdam UMC/GGZ inGeest), Nijmegen (Radboudumc/ProPersona, with MRI scans at Donders Center of Cognitive Neuroimaging), Maastricht (Maastricht UMC+/Mondriaan groep, with MRI scans at Scannexus), and Eindhoven and Groningen (2 sites of neurocare clinics). Participants from Eindhoven and Groningen undergo MRI scans in either Amsterdam or Nijmegen, based on their preference. The 5 centers aim to contribute equally to patient inclusion (between 35‐60 participants per site). The following rTMS machines are used in this trial: Magstim rapid2 (Amsterdam UMC, Radboudumc, Maastricht UMC+) and Deymed XT 35 (neurocare Eindhoven and Groningen).

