### Randomization

Participants are randomized in a 2:1 ratio to one of 2 treatment arms, with twice as many participants allocated to receive active stimulation of the pre-SMA compared to sham rTMS. This unequal allocation was chosen to maximize the number of participants receiving the active intervention and to enhance recruitment by increasing the probability of assignment to active treatment.

Randomization is stratified by study sites to ensure balanced allocation across centers. Randomization sequences are generated using Castor EDC. Each site implements block randomization using randomly permuted blocks of size 6 to maintain allocation balance within each center and minimize group size imbalances that may arise due to site-specific factors, such as varying levels of experience with rTMS.

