### Outcome Measures

Primary outcome and primary endpoint:

The primary outcome is the severity of OCD as measured by the Yale-Brown Obsessive-Compulsive Scale I (Y-BOCS-I) [34]. The primary endpoint is the difference between the active and sham intervention groups in posttreatment severity of OCD, estimated using an analysis of covariance (ANCOVA) model that adjusts for pretreatment severity of OCD. The intervention effect will also be reported as a standardized mean difference.

Secondary outcomes - clinical:

Response (=35% reduction on Y-BOCS I) [44].Remission (Y-BOCS I<12) [44].The severity of OCD, as measured using the newer version of the Yale-Brown Obsessive-Compulsive Scale - Y-BOCS II [37,45]. A combined version of the Y-BOCS I and II is administered pretreatment and posttreatment. Additionally, Y-BOCS-II severity scores are collected weekly during treatment and at all follow-up sessions, enabling comparison between the 2 versions and potentially supporting further implementation of the newer Y-BOCS II.The clinical global impression (CGI) severity scale [46].Comorbid depression symptoms, measured using the Beck Depression Inventory (BDI) at baseline, posttreatment, and follow-up [47]. In addition, we administer a VAS for depression at these same time points, plus every week during treatment, to monitor treatment response on mood. The simultaneous administration of VAS and BDI at baseline and posttreatment will allow us to scale and validate the VAS relative to the BDI, while offering a much quicker and simpler assessment for the participants.Anxiety, measured using the Beck Anxiety Inventory (BAI) and a VAS, following the same procedure and rationale as for depression [48].For participants with comorbid tics, as identified using the Yale Global Tic Severity Scale (YGTSS) [49], tic severity will be assessed using the same scale.Tolerability of the treatment and side effects, using an in-house questionnaire developed as part of our previous TIPICCO trial [19].

Secondary outcomes - cost-effectiveness

Societal costs will be measured using the iMTA Productivity Cost Questionnaire (iPCQ) [50] and the iMTA Medical Consumption Questionnaire (iMCQ) [51].QoL (EQ-5D-5L) [52]. Quality-adjusted life-years (QALYs) are the most important outcome measure for health care decision makers when deciding about the reimbursement of health care interventions.

Secondary outcomes - neuroplasticity:

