### Sample Size Calculations

Meta-analyses [41,42] suggest an average effect size of 0.71‐0.79 (Hedges’ g) for the effect of rTMS as monotherapy. Our own meta-analysis [8] showed a lower Hedges’ g of 0.50. We use rTMS in addition to intensive 4-week daily ERP, and we therefore conservatively lowered the expected effect size to 0.4, in line with, for example, the augmentative effect of antipsychotics to either SSRI or cognitive behavioral therapy [59]. The effect size 0.4 corresponds to a pre-post intervention decrease in Y-BOCS I score of 4 points, which we consider a minimal clinically important difference (MCID). Our design uses a 2:1 randomization across the 2 conditions, with twice as many participants in the verum rTMS group. Using a significance level of alpha=.05, a 2-tailed comparison between means, and an estimated power of 0.8, the study requires 150 participants in the verum-rTMS arm and 75 in the sham-rTMS arm. Assuming a 10% dropout rate, we will include (225/0.9=) 250 participants. Participants are considered dropouts if they complete less than 60% of the minimum required 20 rTMS+ERP sessions, corresponding to fewer than 12 sessions. We apply stratified block randomization, with study center as the stratification factor, to ensure balanced allocation of conditions across centers. Although we will take the stratified design into account when analyzing the data by using it as a covariate, we will ignore its effect on the required sample size [60].

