#### Secondary Study Parameters- Clinical

Of the clinical secondary outcomes, response (≥35% reduction in Y-BOCS I) and remission (Y-BOCS I ≤12) will be investigated using generalized linear mixed models (LMM, mixed-effects logistic regression). Pre-to-post changes in Y-BOCS II, CGI score, QoL, depression, tics, and anxiety will be tested using LMM analysis for repeated measures. The model will include fixed effects for time, study center, and the group-by-time interaction, but not for the group indicator alone, in order to adjust for potential baseline differences in the outcome variable. The group-by-time interaction term represents the between-group intervention effect and therefore constitutes the primary parameter of interest. Tolerability and side effects will be reported as absolute numbers and described qualitatively.

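### The primary ANCOVA is specified inconsistently: both definitions name only baseline Y-BOCS I, although the sample size section promises the stratification factor, study center, as a covariate.

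*Protocol article*

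**What the plan says.** The protocol article touches on this in five sections.

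- **Randomization:** "Randomization is stratified by study sites to ensure balanced allocation across centers". Within sites, "Each site implements block randomization using randomly permuted blocks of size 6".
- **Sample Size Calculations:** the factor is named again ("We apply stratified block randomization, with study center as the stratification factor"), followed by the analysis commitment: "Although we will take the stratified design into account when analyzing the data by using it as a covariate". The same sentence adds that stratification is disregarded when the trial is sized.
- **Outcome Measures, primary endpoint:** the group difference is "estimated using an analysis of covariance (ANCOVA) model that adjusts for pretreatment severity of OCD".
- **Statistical Analyses, Primary Study Parameter:** "This effect will be estimated using an ANCOVA model adjusting for baseline Y-BOCS I scores".
- **Secondary Study Parameters - Clinical:** for the repeated-measures mixed model, "The model will include fixed effects for time, study center, and the group-by-time interaction".

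Center is thus promised in general terms, listed explicitly for a secondary model, and not named in either description of the primary model.

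**The concern.** An analyst working from Primary Study Parameter would fit treatment and baseline. One working from Sample Size Calculations would add center. The two fits give different standard errors and P values for the same confirmatory test, and nothing in the article says which governs.

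The difference is not purely cosmetic. Blocking within center largely removes between-center variation from the treatment contrast. A model without center still counts that variation as residual error, so its standard error exceeds the true sampling variability whenever center is prognostic. The confidence interval is then wider than it need be and some power is lost.

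The article gives grounds for expecting some center effect. It justifies stratification by site-specific factors such as experience with rTMS, uses two makes of stimulator, and reports uneven progress across sites. It does not say how large the effect is. A choice between two documented models that is made after unblinding would also be open to challenge.

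**Working it through.** **1. The plan's own sample size.** Inputs from Sample Size Calculations: standardized effect 0.4, two-sided alpha 0.05, power 0.80, allocation 2:1, dropout 10%.

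Sham arm: n = (1.96 + 0.842)² × (1 + 1/2) / 0.4² = 7.85 × 1.5 / 0.16 = 73.6, so 74 sham and 148 active (222). The t-test version gives 74.2, so 75 and 150 (225). Then 225 / 0.9 = 250. The stated figures reproduce, and this point does not change them.

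Power at 75/150: SE = √(1/75 + 1/150) = 0.1414; 0.4 / 0.1414 = 2.828; Φ(2.828 − 1.96) = 0.807 (0.804 by t-test).

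**2. Effect of leaving center out.** Let s be the share of outcome variance, after baseline adjustment, that lies between centers. The article gives no value, so s is an assumption shown as a range. Residual variance before removing center is set to 1.

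- With center, the standard error shrinks by √(1 − s). Without center, the model SE is too large by the factor 1/√(1 − s).
- Actual type I error without center is about 2 × [1 − Φ(1.96/√(1 − s))].
- Actual power without center is about Φ((2.828 − 1.96)/√(1 − s)); with center it is Φ(2.828/√(1 − s) − 1.96).

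| Assumed s | SE inflation | Type I error without center | Power without center | Power with center |
|---|---|---|---|---|
| 0 | 0% | 5.0% | 80.7% | 80.7% |
| 0.02 | 1.0% | 4.8% | 81.0% | 81.5% |
| 0.05 | 2.6% | 4.4% | 81.4% | 82.7% |
| 0.10 | 5.4% | 3.9% | 82.0% | 84.6% |
| 0.20 | 11.8% | 2.8% | 83.4% | 88.5% |

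These are large-sample approximations that treat the arms as exactly balanced within center. The row at 0.20 is an upper extreme, not an expectation.

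**3. Check by simulation.** Set-up: five centers (60/45/40/40/40, total 225), permuted blocks of 6, 2:1 allocation, 4,000 trials per scenario. The center sizes are assumed; the article gives a target of 35 to 60 per site and no counts.

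- Ratio of model SE without to with center: 1.000, 1.010, 1.026, 1.055 and 1.119 for s = 0, 0.02, 0.05, 0.10 and 0.20.
- At s = 0.20 the model SE without center was 0.142, against an actual spread of the estimates of 0.129.
- Type I error without center: 5.2%, 5.1%, 4.3%, 4.8% and 3.5%. The simulation error is about 0.3 points (√(0.05 × 0.95 / 4000)), so the small differences from the table at low s should not be over-read.
- Power without against with center: 80.4% and 82.0% at s = 0.05; 81.4% and 84.4% at s = 0.10.

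Formula and simulation agree closely on the standard error. They put the power given up at roughly 1 to 3 points for s between 0.05 and 0.10, and at about half a point for s = 0.02.

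**The case against.** The strongest reply is that the plan already includes center. The commitment closes the section that sizes the trial for the between-arm comparison, so its natural reach includes the primary analysis. Neither definition of the primary model uses a word such as only, and no section excludes center. On that reading there is one plan, described briefly in two places. The article is also a condensed document, and it says that analysis plans will be preregistered.

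Much of this stands. A reader might infer that the trial will adjust for baseline alone and that its primary standard error is therefore too wide. The documents do not support that: it requires center to be left out despite the stated commitment, and also to be prognostic, for which no variance is given. A reader might also infer that the primary model is the only efficacy model without center. That is not established either. It is unclear whether the sentence listing center covers the logistic models for response and remission, and the regressions under Cost-Effectiveness name no center term.

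On consequences, the objection is right that the error is conservative, that planned power of 80% is still met in every row of the table, and that the precision at stake was never counted on when the trial was sized.

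What does not stand is that this is merely unstated detail. The article states the primary covariates twice, makes a wider commitment elsewhere, and lists center for a secondary model. Those statements do not match, and the mismatch concerns the confirmatory test.

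**Conclusion.** The point holds as an inconsistency in how the primary model is specified. It is not a demonstrated error in the primary standard error. If the Primary Study Parameter sentence were implemented literally, the model SE would be inflated by about 0%, 1%, 2.6% or 5.4% for center shares of 0%, 2%, 5% or 10%. The test would be mildly conservative, with no inflation of type I error, no bias in the treatment estimate and no change in the required sample size. The size rests entirely on the assumed center share; if center is not prognostic, nothing is lost. Severity is low to moderate: worth correcting because it settles the confirmatory model in advance at almost no cost, but not something that must be fixed for the trial to be valid.

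**What to change.** Before unblinding, use one and the same definition under Outcome Measures and under Primary Study Parameter: an ANCOVA of posttreatment Y-BOCS I on treatment group, baseline Y-BOCS I and study center, with center as a five-level fixed effect. Carry the same wording into the preregistered analysis plan. Under Secondary Study Parameters - Clinical, state that the models for response and remission also include center.

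This puts into effect what Sample Size Calculations already promises. It costs a few words and four degrees of freedom out of about 225 analyzed participants, and needs no change to the sample size or to data collection. Posttreatment assessments are due to finish in December 2026, so there is time to do it.

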## Discussion

### Anticipated Findings

This study protocol outlines the first adequately powered multicenter RCT investigating the efficacy and cost-effectiveness of the pre-SMA-rTMS protocol compared to sham-rTMS as adjuvant therapy to ERP in adults with OCD who did not adequately respond to prior first-line treatment. The RCT aims to assess both the clinical efficacy and cost-effectiveness of rTMS targeting the pre-SMA in this population. Alongside the primary focus on efficacy and cost-effectiveness, the study also incorporates several exploratory biological outcome measures designed to shed light on the mechanisms underlying variation in treatment response and short- and long-term treatment-induced neuroplasticity. These measures may ultimately contribute to identifying and developing biomarkers that can inform treatment decisions beyond standard clinical assessments.

It is hypothesized that rTMS combined with ERP will be more efficacious and cost-effective compared to sham-rTMS and ERP. Additionally, we also expect clinical effects (Y-BOCS reduction) in the sham-rTMS group, as both groups receive an intensive format of ERP at expert centers for OCD. The clinical outcomes in the verum group may be comparable to those observed in our previous TIPICCO trial (Clinical Trial ID: NCT03667807 [19], which demonstrated a significant reduction in symptoms (Cohen *d*=1.66, Δ Y-BOCS = −10.836, *P*<.001, 95% CI −12.504 to −9.168) and a 57.4% response rate across 3 different rTMS protocols combined with ERP in a comparable participant group. Participants in that trial received fewer treatment sessions (16 vs 20‐28), shorter ERP sessions (60 vs 90 min), and different TMS protocols (eg, 10 Hz pre-SMA); however, this may allow for improved outcomes in this study.

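### Under 2:1 allocation the primary ANCOVA should name a heteroscedasticity-consistent standard error, because the default pooled one is miscalibrated if the arms differ in residual spread

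*Protocol article*

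**What the plan says.** The primary analysis is described twice in the Protocol article. Outcome Measures defines the endpoint as the posttreatment difference between arms, "estimated using an analysis of covariance (ANCOVA) model that adjusts for pretreatment severity of OCD". Primary Study Parameter repeats it: "This effect will be estimated using an ANCOVA model adjusting for baseline Y-BOCS I scores". Sample Size Calculations adds that study center will be a covariate. None of these places mentions a pooled variance, a model-based standard error, a robust standard error or arm-specific residual variances.

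Allocation is unequal: "Participants are randomized in a 2:1 ratio to one of 2 treatment arms" (Randomization). The sample size rests on one standardized effect, "we therefore conservatively lowered the expected effect size to 0.4", tied to 4 Y-BOCS I points, and concludes that "the study requires 150 participants in the verum-rTMS arm and 75 in the sham-rTMS arm". No SD is given by arm. The Dissemination Plan says that analysis plans will be preregistered on the Open Science Framework; that plan is not shown.

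**The concern.** Ordinary ANCOVA estimates one residual variance from both arms together. With equal arms, its standard error for the treatment difference stays almost exactly right even when the spreads differ. With two verum participants for every sham participant that protection is lost. The pooled variance is weighted about two-thirds to verum, while the smaller sham arm supplies most of the sampling error. If verum outcomes are less spread out than sham, the standard error is too small and the interval too narrow. If they are more spread out, the standard error is too large and power is lost.

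The trial itself takes an interest in "the mechanisms underlying variation in treatment response" (Anticipated Findings), so a difference in spread is possible, although its direction cannot be known in advance. This is the only primary test. Its interval will be read against the 4-point difference that the article treats as clinically important, and the results may feed the reimbursement decision.

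**Working it through.** **Inputs from the article (Sample Size Calculations):** n₁ = 150 verum, n₀ = 75 sham, two-sided alpha 0.05, power 0.8, standardized effect 0.4, dropout 10%. **Assumption, not in the article:** r = residual SD in verum ÷ residual SD in sham, examined from 0.7 to 1.25, with the sham SD set to 1.

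**1. The plan's own figure.** With a common SD of 1, SE² = 1/150 + 1/75 = 0.0200, so SE = 0.1414 and 0.4/0.1414 = 2.83. Power = Φ(2.83 − 1.96) ≈ 0.807 (0.804 with the t distribution). 225/0.9 = 250. The stated sample size reproduces.

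**2. Standard error under unequal spread.**

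- Pooled variance = (149r² + 74)/223.
- Model SE² = pooled variance × (1/150 + 1/75).
- True SE² = r²/150 + 1/75.
- Actual alpha = 2 × [1 − Φ(1.96 × model SE/true SE)]; coverage = 1 − alpha.

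Example, r = 0.8: pooled variance = (149 × 0.64 + 74)/223 = 0.7595. Model SE² = 0.7595 × 0.02 = 0.01519. True SE² = 0.64/150 + 1/75 = 0.01760. SE ratio = √(0.01519/0.01760) = 0.929. Alpha = 2 × [1 − Φ(1.821)] = 0.069.

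| r (verum/sham) | Model SE ÷ true SE | Actual alpha | 95% CI coverage |
|---|---|---|---|
| 0.7 | 0.891 | 8.1% | 91.9% |
| 0.8 | 0.929 | 6.9% | 93.1% |
| 0.9 | 0.965 | 5.9% | 94.2% |
| 1.0 | 1.000 | 5.0% | 95.0% |
| 1.1 | 1.032 | 4.3% | 95.7% |
| 1.25 | 1.076 | 3.5% | 96.5% |

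**3. Is the allocation the cause?** The same formula at 112 and 113 per arm, with r from 0.67 to 1.5, keeps alpha between 4.96% and 5.04%. So the unequal allocation is what makes the variance assumption matter.

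**4. Simulation with a baseline covariate** (150:75, correlation 0.5, 20,000 runs). At r = 0.8, 1 and 1.25 the pooled standard error rejects in 6.7%, 4.9% and 3.4% of runs with equal means. HC3 rejects in 4.9%, 4.9% and 4.8%.

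**5. Power.** Power = Φ[(δ − 1.96 × SE used)/true SE], with the true SE as the one used for the robust column. With unequal SDs, the effect 0.4 must be tied to one of them; both choices are shown.

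| r | 0.4 scaled to | δ | Pooled SE | Robust SE |
|---|---|---|---|---|
| 1.25 | pooled SD | 0.469 | 82% | 86% |
| 1.25 | sham SD | 0.400 | 69% | 74% |
| 0.8 | pooled SD | 0.349 | 79% | 75% |
| 0.8 | sham SD | 0.400 | 88% | 85% |

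At r = 1 the formula gives no difference. HC3's small-sample cost appears in simulation (40,000 runs): 80.3% with the pooled standard error and 79.7% with HC3, about 0.5 points.

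**The case against.** Four objections deserve an answer.

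**The article never says equal variance.** This stands. An HC3 standard error is compatible with every sentence on the primary analysis, and the estimator is the sort of detail that the unseen preregistered plan may settle. A reader might infer that the trial has committed itself to a faulty test; the text supports only that the method as named defaults to the pooled form.

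**No spread by arm is documented.** This also stands. A reader might take the interest in differential response as evidence that the spreads will differ. But the article expects improvement under sham plus ERP as well, and looks for predictors of response to ERP alone and to the combination. Heterogeneity in both arms says nothing about the ratio between them. At ratios of 0.9 to 1.1 alpha is only 5.9% to 4.3%.

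**Inflated alpha does not mean false claims for an inert treatment.** Correct. If rTMS changes nobody's outcome, both arms have the same distribution and the P value is valid. The figures above 5% need rTMS to narrow the spread while leaving the mean unchanged, and nothing in the article suggests that. If rTMS narrows the spread by moving many people toward remission, the mean moves too and rejecting is right. The interval would still be too narrow.

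**If verum is more variable, the test is merely conservative.** True for alpha. Whether the lost power matters depends on scaling: with the pooled standard error it is 82% if 0.4 refers to the pooled SD, but 69% if it refers to the sham SD. The robust standard error recovers about 4 to 5 points in either case.

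**Conclusion.** The point holds as a conditional weakness of the method as named. Under 2:1 allocation the default ANCOVA standard error is miscalibrated if the residual spread differs between arms, in either direction. For assumed verum/sham SD ratios of 0.7 to 1.25, coverage of the 95% interval runs from about 92% to 96.5%, and alpha for the test of equal means from about 8% to 3.5%. The treatment estimate is not biased by unequal variance, and the planned 225 evaluable and 250 randomized participants stand.

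A reader might conclude that the planned P value and interval are wrong. The documents do not support that: they give no arm-specific SDs and do not state the pooled form, and a treatment with no effect on anyone leaves the P value valid. What remains is mainly interval coverage, and power if verum is the more variable arm. It is worth fixing because the remedy is cheap and should be chosen before the spreads by arm are seen. It is an improvement, not the correction of a demonstrated error.

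**What to change.** Before unblinding, add one sentence to the analysis plan: the primary ANCOVA keeps its point estimate, and its standard error, 95% confidence interval and P value come from a heteroscedasticity-consistent (HC3) covariance matrix.

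For the continuous secondary outcomes, the linear mixed models may use arm-specific residual variances. This does not carry over to the logistic mixed models for response and remission, which have no free residual variance. The two devices are not interchangeable: arm-specific variances reweight the fit and can move the estimate, which is why HC3 is proposed for the primary analysis.

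The cost is about 0.5 points of power if the variances are equal. If verum is less variable, nominal power falls (for example from 79% to 75% at a ratio of 0.8 with 0.4 scaled to the pooled SD). That is a proper correction, because the pooled standard error would overstate precision there. The sample size does not change. Posttreatment assessments are expected to finish by December 2026, so there is time to add the sentence.
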